## Abstract

**Background:**

Despite the existing national and international plans of action to end violent discipline strategies used by teachers in schools, they still prevail in Tanzanian schools. This underlines the need to implement school-based interventions that aim at reducing violent discipline by teachers. In this study, we will evaluate the feasibility and effectiveness of the preventative intervention *Interaction Competencies with Children – for Teachers (ICC-T)* in Tanzanian primary schools. Following its success in secondary schools, we hypothesize that the intervention will reduce teachers’ positive attitudes towards and their use of violent discipline at school.

**Methods/design:**

The study will be conducted in six randomly selected regions in Tanzania. We have already randomly selected two schools in each region (12 in total) that fulfill our inclusion criteria. From each region, one school will be randomly assigned to the intervention and the other to the monitoring group (no intervention). Eighty students between the ages of 9 to 12 years (*N* = 960) and 20 teachers from each school (*N* = 240) will be included in the trial. We will collect data directly before the intervention (t1) and 6 months after the intervention (t2) both at intervention and monitoring schools. Using guided questionnaire assessments, we will measure violence by teachers using students’ reports on their exposure to and teachers’ reports on their use of violence using the Conflict Tactics Scale. Furthermore, we will assess teachers’ positive attitudes towards violent discipline using a modified version of the Conflict Tactic Scale. The feasibility of the intervention will be evaluated using purpose-built measures assessing the demand, applicability, acceptability, and integration of core elements into daily work in the participating schools.

**Discussion:**

The proposed study will allow us to test the feasibility and effectiveness of an intervention aiming to reduce positive attitudes towards and the use of violent discipline by teachers in school settings. With the reduction of violent discipline by teachers, this study contributes to national and international efforts towards ending violence against children as well as the attainment of the United Nations’ Sustainable Development Goals that also aim to prevent all types of maltreatment of children.

**Trial registration:**

ClinicalTrials.gov, NCT03893851. Registered on 28 March 2019.

## Background

Violent discipline by teachers at school entails the use of different forms of physical and emotional acts that violate children’s dignity and inflict pain with the intention of correcting a child’s misconduct [1]. Violent discipline takes diverse forms, including the use of hands or objects, such as a cane, whip, or stick, by teachers and school staff [2]. Despite the existence of different national and international intervention strategies to end violent discipline by teachers, the prevalence of the use of violent discipline by teachers is still reported globally [3–5]. In many countries in Sub-Saharan Africa, including, for example, Tanzania, violent discipline by teachers is still legal and considered by teachers as being a necessary and effective disciplinary tool to control student behavior [6].

### Global perspective on violence by teachers at school

Previous research has indicated that violence against children in schools is a critical global problem [7]. Straus [8] reported that millions of children worldwide experience violence at school. For example, the prevalence of violence by teachers ranged from 34% to 93% in India, from 7% to 51% in Peru, from 1% to 50% in Vietnam, from 12% to 76% in Ethiopia, and was reported to be 58% in Jamaica and 56% in Yemen [9–11]. These findings stand in direct contrast to the aims of the United Nations’ Convention on the Rights of the Child [12], which outlines the “protection of the physical and mental integrity of all children”, as well as of the United Nation’s Sustainable Development Goal No. 16.2 [13] which aims to “end all forms of violence against children”. Nevertheless, Zolotor and Puzia [14] and the Global Initiative to End All Corporal Punishment against Children [3] reported that corporal punishment and other forms of violence against children in a school setting are legally prohibited in 128 countries while 69 countries still legally accept such violent actions as a means of controlling students’ misconduct at schools, leaving slightly more than two billion children worldwide without full legal protection.

Reports of violence against children in Africa differ significantly from one country to another [15]. In Uganda, for instance, the use of harsh discipline is prevalent among teachers in schools despite the prohibition by law [16]. Exposure to teachers’ violent discipline was reported by 86% of girls in Kenya, 82% in Ghana, and 66% in Mozambique [17]. In Uganda, school children are reportedly at high risk of all forms of violence, particularly physical and emotional violence by school staff [18]. In Tanzania, UNICEF [19] reported that one out of two children reported having experienced physical violence at the hands of teachers. For example, children were frequently beaten and even burnt by their teachers [20]. A recent study of a national representative sample of Tanzanian secondary school students reported that almost every student experienced physical and/or emotional violence by teachers. This very high prevalence was reported both by students and teachers [5, 21].

### Factors influencing the use of violent discipline by teachers

The use of violent discipline at school in many of these countries can be attributed to a number of factors, including large classes and inadequate training in how to interact non-violently with students [16]. In fact, the teaching and learning environment in East Africa is a harsh one currently, with stressed and burdened teachers, poor teacher–student ratios, and limited classroom infrastructure, all of which seem to increase the likelihood of teachers employing violent discipline strategies [1, 5, 6, 22]. Hecker et al. [5] reported that teachers’ stress as well as lack of alternative disciplining strategies among teachers intensified the use of violent discipline among teachers. Furthermore, Meyer and colleagues [23] reported that a lack of a positive school environment and children’s exposure to community violence—which itself was linked to adverse mental health outcomes—were associated with the use of violent discipline by teachers at school in low income countries, such as Tanzania. Furthermore, teachers’ beliefs, poor working conditions, and problems in teacher–student interactions increased teachers’ use of violent discipline [6]. Moreover, Semali and Vumilia [24] put forth that teachers considered the use of violent discipline as an accepted norm. Teachers are reported as believing that violent discipline is a useful method for creating an orderly learning environment, developing good conduct, maintaining safe school behaviors, enforcing discipline, and improving academic performance. Teachers justify the use of violence in the context of child discipline procedures and as a way of exercising power, compliance, and behavioral control [25]. Cheruvalath and Tripathi [26] argue that a lack of proper training on how to manage students and a poor understanding of the consequences of violence for school children may significantly increase the use of violent discipline by teachers. In addition, violence against children in Tanzanian school settings is still high due to the legalization of violent discipline [1, 5] as well as the social acceptance of violent discipline in the community at large and by teachers specifically [6, 27].

### Effects of violence on child development

The learning environment should be free of fear and violence to ensure children’s healthy physical, mental, social, emotional, and cognitive development, which together contribute to the academic performance of students [28]. The socio-ecological theory explains children’s development as a process embedded within multiple contexts, which include families, schools, and communities [29]. Therefore, it is important to examine school contexts to better understand the effects of violence by teachers. In schools, the high prevalence of violence affects students in all grades [29, 30]. For example, school violence is associated with lower academic performance [31–34], impacts children’s cognitive development [35–37], and is related to mental health problems [31, 34, 38–40]. Furthermore, children experiencing violence and maltreatment in schools displayed significantly higher levels of psychological problems, including depression, loneliness, anxiety, reinforcement of negative self-evaluations, and fear or avoidance of social interactions and, as a result, they increasingly became targets of bullying by peers [40–42].

### Global intervention strategies to end violence against children

Globally, different initiatives have been carried out in an effort to protect children from violence. The United Nations General Assembly [12] set the agenda to end all forms of violence against children almost 30 years ago. Article 19 of the United Nations Convention on the Rights of the Child calls for the protection of children from all forms of physical or emotional violence, injury, or abuse by any person in any setting. Article 28 requires parties to take all appropriate measures in ensuring that the behavior of children in schools is managed in a manner consistent with the child’s human dignity [12]. Moreover, the Global Initiative to End All Corporal Punishment against Children [43] aims to eliminate violence against children in all settings and goes hand in hand with UN Sustainable Development goal No.16.2.

Besides initiatives that aim at contributing to legal and political changes, very few school-based intervention strategies that aim to reduce the use of violent discipline in school settings have been implemented and even fewer have been scientifically evaluated in Sub-Saharan Africa. In Uganda, for example, the Good Schools Toolkit, which includes different activities for staff, students, and administration, focused on improving the school compound and creating a better learning environment, respect and understanding power relationships, improving teaching techniques, creating accountability, and learning non-violent methods of discipline. The intervention has been used in primary schools and its effect on overall levels of ‘any’ form of violence (physical, emotional, sexual combined) from school staff and/or peers has been reported [16, 44, 45]. Another example is the intervention approach Stop Violence Against Girls in Schools that was carried out by Action Aid in Ghana, Kenya, and Mozambique. The intervention program showed significant results: the use of caning by teachers dropped by 23% in Mozambique while girls enrolment increased by 14%, 17%, and 10% in Ghana, Kenya, and Mozambique, respectively [46].

### Intervention to end violence by teachers against children in Tanzania

In Tanzania, severe forms of violence against children in school settings are generally prohibited by the Law of the Child Act [47], which states: “A person shall not subject a child to torture, or other cruel, inhuman punishment or degrading treatment including any cultural practice which dehumanizes or is injurious to the physical and mental well-being of a child ….”*.* Moreover, the Corporal Punishment Guideline [48, 49] set limits to the number of strokes from six to four and gives mandate to the Head of School to administer the punishment. Additionally, the guideline directs the Head of School to document details of the student being punished to include, among other details, names and the misbehavior committed. However, in reality we find differences in implementation of the legal guideline as teachers administer corporal punishment without compliance to the law and the guideline [49].

Apart from the legal intervention strategies, the school-based preventative intervention approach *Interaction Competencies with Children – for Teachers* (*ICC-T*) has been evaluated in a cluster randomized controlled trial (CRCT) in secondary schools and in a pilot study with one selected primary school in Tanzania [1, 6]. *ICC-T* is based on attachment, behavioral, and social learning theories. The key principles are the intervention’s feasibility in low resource contexts, a participatory approach, and practical orientation. *ICC-T* aims to enable teachers to use non-violent disciplinary measures and to strengthen their competencies in non-violent interactions by introducing essential interaction competencies with children into the daily work of teachers. The pilot study demonstrated the feasibility of *ICC-T* at the primary school level [6] and the CRCT provided initial evidence of the effectiveness of the preventative intervention at the secondary school level: The use of violent discipline by teachers (self-reported and reported by students) was reduced in the intervention schools compared to control schools. Furthermore, teachers in the intervention schools reported less positive attitudes towards the use of violent discipline in intervention schools at follow-up compared to control schools [1]. Participating teachers in intervention schools reported a high acceptance of the intervention and a good integration of *ICC-T *content into their daily work.

### Study objective

Based on the lack of evidence for school-based interventions — particularly at the primary school level — that effectively reduce violence utilized by teachers, we advocate for conducting controlled intervention studies to reduce the use of violent discipline by teachers in primary schools. Reducing violence against children in education settings requires intervention strategies that also target a change in common societal beliefs and attitudes that the community holds towards violent discipline. Due to the legalization of violent discipline in Tanzanian schools under the National Corporal Punishment Regulations pursuant to article 60 of the National Education Act [48, 49], positive attitudes are still associated with the use of violent disciplinary methods. Furthermore, teachers lack non-violent action alternatives. Therefore, there is a pressing need to implement preventative intervention approaches and to conduct controlled studies aiming to reduce the use of violent discipline by teachers in primary schools in Tanzania. Embarking on the success of *ICC-T* in secondary schools in Tanzania [1], in this study we therefore aim to test the feasibility and effectiveness of *ICC-T* in primary schools. We therefore hypothesized that the implementation of *ICC-T* will reduce both positive attitudes towards and the use of violent discipline by teachers in primary schools in Tanzania.

## Methods/design

### Design of the study

Using a two-arm matched cluster randomized controlled trial, the study will include 12 schools from six regions in Tanzania. From each region one school will be randomly allocated to the intervention school condition (from which all teachers will be trained in an ICC-T intervention workshop) and the other to the monitoring school condition (which receive no intervention). The study will have two data collection phases: pre-assessment directly before the intervention (t0) and follow-up assessment approximately 6 months after intervention (t1). See Figs. 1 and 2 and the SPIRIT 2013 Checklist: Recommended items to address in a clinical trial protocol and related documents (Additional file 1).

**Fig. 1 Fig1:**
[figure not shown]
Flow chart of the study design

**Fig. 2 Fig2:**
[figure not shown]
Participant time line chart

### Study setting

This study will be carried out in public primary schools in Tanzania. In total, five regions have been randomly selected to represent the five administrative zones: Central-Western Lake Zone, Eastern and Coast Zone, Lake Zone, Northern Zone, and Southern Highland Zone*.* Using http://www.random.org, the regions Tabora, Mtwara, Shinyanga, Tanga, and Njombe have been randomly selected, respectively, to represent the aforementioned zones. In addition, the Dar es Salaam region will be studied due to its unique population characteristics and its significant number of schools, teachers, and students at the primary school level [50]. The selection of the regions ensures representation of the country geographically, economically, socially, and politically. From each region, two districts were randomly selected: Igunga and Urambo from Tabora region; Mtwara and Newala from Mtwara region; Kishapu and Shinyanga from Shinyanga region; Korogwe and Tanga from Tanga region; Njombe and Wanging’ombe from Njombe region; and Kinondoni and Temeke from the Dar es Salaam region.

### Schools

One public primary school from each selected district will be randomly selected, resulting in a total of 12 schools. Only public primary schools with more than 40 students per enrolment year will be included in the study. The list of schools with the specified criteria was obtained from the National Examination Council of Tanzania [51]. The number of students who sat the primary school leaving exam in each of the respective district’s schools implied their enrolment rate. Schools that qualified for the criteria in each district will be listed in alphabetical order and a random selection of one school from each district will be executed using http://www.random.org.

### Participants

We will assess children and teachers at pre-assessment and at follow-up assessment. In addition, feasibility data of teachers participating in intervention trainings will be assessed at the beginning and the end of the *ICC-T* training workshops as well as at follow-up assessment. We aim to include students from the fifth and sixth years of formal schooling. Students’ ages will range between 9 and 12 years. This age group is selected because of its ability to comprehend the questionnaire items and its availability during follow-up assessment (students in the seventh year of formal schooling will shift to secondary school before the follow-up assessment can be completed). All teachers employed at the selected schools will be eligible to participate in the study (Fig. 1).

Within each of the selected schools, 40 pupils from of the fifth and 40 pupils from sixth year of formal schooling will be stratified by gender and then randomly selected. Thus, the target sample will be 960 pupils. Based on a study that used a similar design [1], we would expect moderate to large effects on pupils’ self-reported exposure to violence. An a priori power analysis (α = 0.05, power = 0.80, moderate effect size of ƒ = 0.25) indicated a required total sample size of at least *n* = 128 pupils to detect significant interaction effects. To adjust for the nested design of the study, we calculated the following design effect (DE): DE = 1 + (fixed cluster size considering drop-outs − 1) × intra-cluster correlation coefficient. Considering 80 pupils per school, a dropout rate of 20%, and an intra-cluster correlation coefficient of 0.05, the DE for the pupil sample is 4.15, which results in a required sample size of at least 532 pupils. All teachers at the selected schools will be included in the study sample. Our target sample will be at least 20 teachers per school, resulting in a total sample of at least 240 teachers. Based on the previous study, we would also expect moderate to large effects on teachers’ self-reported use of violence against students. The a priori power analysis (see above for details) indicated a required total sample size of at least *n* = 128 teachers to detect significant interaction effects. To adjust for the nested design of the study, we again calculated the DE. Considering a minimum of 20 teachers per school, a drop-out rate of 20% and intra-cluster correlation coefficient of 0.05, the DE for the teacher sample is 1.8, which results in a required sample size of at least 231 teachers.

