### Data analysis

Pre-assessment data will be used to provide information about the prevalence of maltreatment and violence in different settings as well as children’s mental health and well-being. Longitudinal analysis will be carried out based on the groups as randomized (intention to treat). We will use the last-observation-carried-forward approach; i.e., in drop-outs we assume no change from pre-assessment to follow-up. Results will be presented including appropriate effects sizes and with a measure of precision (95% confidence intervals). Our main analysis of the primary and secondary outcomes will be time × group interaction effects using repeated multivariate analysis of variance (MANOVA). In case of a noted cluster effect (intra-cluster correlation coefficient > 0.10) we will use multilevel analysis. Multivariate interaction effects and univariate interaction effects of each outcome variable will be tested first. Paired *t*-test analysis will examine the differences from the pre- to follow-up assessment in the intervention group while independent *t*-test will examine whether there is a difference between the control group and intervention group at the follow-up assessment. Effect size η^2^ ≥ 0.01, η^2^ ≥ 0.06 and η^2^ ≥ 0.14 will be considered to represent a small, moderate, and large effect, respectively [57]. For *t*-tests, effect size interpretation will be guided by the suggestion of Cohen where d ≥ 0.20, d ≥ 0.50, and d ≥ 0.80 will represent a small, medium, and large effect, respectively [57].

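### The sample size corrects the variance for clustering but not the degrees of freedom for 12 schools, so 231 teachers and 532 pupils do not by themselves give the stated 80% power

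*Protocol article*

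**What the plan says.** Under Participants the protocol article gives its inputs as "An a priori power analysis (α = 0.05, power = 0.80, moderate effect size of ƒ = 0.25") and reports that this "indicated a required total sample size of at least *n* = 128 pupils to detect significant interaction effects". The teacher paragraph repeats the figure: "128 teachers to detect significant interaction effects". To allow for nesting it uses "DE = 1 + (fixed cluster size considering drop-outs − 1) × intra-cluster correlation coefficient". For pupils (80 per school, 20% drop-out, ICC 0.05) this gives a design effect of 4.15 and 532 pupils. For teachers the inputs are "Considering a minimum of 20 teachers per school, a drop-out rate of 20% and intra-cluster correlation coefficient of 0.05", and the conclusion is that "the DE for the teacher sample is 1.8, which results in a required sample size of at least 231 teachers". The recruitment targets are 960 pupils and at least 240 teachers.

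The design is fixed under Design of the study: "Using a two-arm matched cluster randomized controlled trial, the study will include 12 schools from six regions in Tanzania". The Discussion puts six schools in each arm. The Data analysis section plans a time × group interaction by repeated-measures MANOVA, and adds: "In case of a noted cluster effect (intra-cluster correlation coefficient > 0.10) we will use multilevel analysis".

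**The concern.** Schools are randomised, so the uncertainty of the group comparison has to be estimated from the variation between 12 schools. A design effect makes the variance larger, but it does not change the reference distribution. The calculation still uses the critical value for about 126 error df (1.98). The critical value is 2.23 on 10 df and 2.57 on 5 df. The number of schools does not enter the power calculation at all, so it holds only for a trial with many clusters.

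Teacher self-report is one of the two measures of the primary outcome. If its power is nearer 66–71% than 80%, the chance of missing the effect planned for is about 30–35% rather than 20%. A null teacher result could then be read as stronger evidence against a moderate effect than it is.

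**Working it through.** **Inputs from the protocol article.** f = 0.25, which is d = 0.5 for two equal groups; α = 0.05, taken as two-sided; power 0.80; ICC 0.05; 12 schools; per school 20 teachers (16 after 20% drop-out) and 80 pupils (64 after 20% drop-out).

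**Reproducing the printed figures.**
- Two-group F test, noncentrality f² × N = 0.0625 × 128 = 8, on 1 and 126 df: power 0.801. N = 127 gives 0.798, so 128 is the smallest N.
- Pupils: DE = 1 + 63 × 0.05 = 4.15; 128 × 4.15 = 531.2, hence 532.
- Teachers: DE = 1 + 15 × 0.05 = 1.75, printed as 1.8; 128 × 1.8 = 230.4, hence 231.

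All the printed figures reproduce, apart from rounding 1.75 to 1.8.

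**Power on school-level df.** With m analysed per school:
- effective N = 12m / DE, where DE = 1 + (m − 1) × ICC
- noncentrality of t = 0.5 × √(effective N / 4)
- power = probability that a noncentral t exceeds the two-sided 5% critical value on 12 − 2 = 10 df, or on 6 − 1 = 5 df for six pairs.

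| Case (ICC 0.05) | DE | Effective N | Noncentrality | Individual df | 10 df | 5 df, no matching gain |
|---|---|---|---|---|---|---|
| 231 teachers, printed DE | 1.80 | 128.3 | 2.83 | 80.2% | 72.4% | 62.4% |
| 532 pupils, printed DE | 4.15 | 128.2 | 2.83 | 80.2% | 72.3% | 62.3% |
| Teachers, 20 per school | 1.95 | 123.1 | 2.77 | 79% | 70.6% | 60.6% |
| Teachers, 16 per school | 1.75 | 109.7 | 2.62 | 74% | 65.6% | 55.9% |
| Pupils, 64 per school | 4.15 | 185.1 | 3.40 | 92% | 86.5% | 77.5% |

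The first two rows isolate the df error: same effective N, about 8 points less power on 10 df. Simulated trials of school means (200,000 per setting) gave 70.5% and 65.6% for the two planned teacher cases on 10 df. The smallest teacher effect detectable with 80% power on 10 df is d = 0.56 at 20 per school and 0.59 at 16.

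**Sensitivity for teachers, 10 df.**
- ICC, 20 per school: 0.02 gives 84.3%, 0.03 gives 79.5%, 0.05 gives 70.6%, 0.10 gives 53.8%.
- Teachers per school at ICC 0.05: 25, 30 and 35 give 75%, 78% and 80%.
- Pre-post correlation r (assumed; the document gives none). If d = 0.5 is in raw-score SDs with equal variance at both times, the change-score effect is 0.5 / √(2(1 − r)). With ICC 0.05 on the change score, power at 20 (16) per school is 63% (58%) at r = 0.4, 71% (66%) at 0.5, 80% (75%) at 0.6 and 90% (86%) at 0.7.
- Matching, 5 df, 20 per school: 60.6% if pairing removes none of the between-school variance, 73.0% if it removes half, 78.9% if it removes 70%. The document states no matching gain.

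**The case against.** The strongest reply is that 71% is not a property of the trial. The planned test is a time × group interaction, and the document does not say on which scale f = 0.25 is defined. A 2 × 2 fixed-effects interaction (1 and 124 df) also has 128 as its smallest N. Read that way, f = 0.25 is a difference in change of 1.0 raw SD. Even at zero pre-post correlation that is 1/√2 = 0.71 SD of the change score, and power at 16 teachers per school and ICC 0.05 is about 91% on 10 df. Stable school differences also cancel in a change score, so its ICC may be below 0.05. And 20 teachers per school is a floor. All of this stands as a reason not to print one replacement figure. It does not remove the error: the 2 × 2 reading has the same noncentrality of 8 at N = 128, so the step from 128 to 231 still leaves individual df in place.

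A second reply is that the planned MANOVA uses individual df. It does, unless the ICC exceeds 0.10. But the plan assumes an ICC of 0.05 and a teacher design effect of 1.8. A test that ignores clustering of that size understates the standard error, and its nominal power is not that of a valid test.

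A third reply is that recruitment is complete and confidence intervals are planned, so little changes. This is fair as to consequence: the remedy is in what is stated and how the comparison is tested.

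**Conclusion.** The point holds in conditional form. The sample-size calculation makes no allowance for 12 randomised schools, so its totals of 231 teachers and 532 pupils do not by themselves secure 80% power. With d = 0.5 and ICC 0.05 taken as applying to the analysed change score, and 20 teachers per school, teacher power on 10 df is about 71% without drop-out and 66% with the plan's 20% drop-out.

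A reader might infer more than the document supports:
- That true teacher power is 71%. It could be higher or lower, depending on the ICC, the pre-post correlation, the scale of f and the number of teachers per school.
- That the pupil comparison is underpowered. On 10 df the planned pupil sample keeps about 86% at ICC 0.05; only the 532 figure falls short.
- That power is about 61% because schools are matched. That assumes matching removes no between-school variance, which the document does not say.
- That the sums are wrong. They reproduce; the fault is using a many-cluster formula for 12 clusters.

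**What to change.** Keep the 12 schools and the planned recruitment. Under Participants:
- Replace the two required totals with the power of the planned sample on school-level df: teachers about 66–71% (with and without 20% drop-out), pupils about 86% (64 analysed per school), and a smallest detectable teacher effect of d about 0.56–0.59.
- State that these take d and the ICC on the change score and 20 teachers per school.
- Show a range over the ICC (at 20 teachers per school without drop-out: 0.03, about 80%; 0.05, about 71%; 0.10, about 54%) and over the pre-post correlation.
- Label any 5-df figure with the matching gain that it assumes.

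Under Data analysis, state that the primary group comparison accounts for schools with school-based df at the assumed ICC of 0.05, and not only when the ICC exceeds 0.10. Otherwise the restated power describes a test that the plan would not run. The particular small-sample method can be left to the analysis plan.

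The cost is a less favourable stated teacher power, a short sensitivity table and one sentence on the analysis. No schools, participants or data are added.

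### The 231 teachers required are analysed teachers, but the plan's own 20% drop-out leaves 192 of 240, so power is about 74%, not 80%

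*Protocol article*

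**What the plan says.** The sample-size text is in the protocol article, Methods/design, Participants. The starting inputs, given for pupils and carried over to teachers, are "α = 0.05, power = 0.80, moderate effect size of ƒ = 0.25". For teachers, "The a priori power analysis (see above for details) indicated a required total sample size of at least *n* = 128 teachers".

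Clustering is then handled by "DE = 1 + (fixed cluster size considering drop-outs − 1) × intra-cluster correlation coefficient". The teacher inputs are "Considering a minimum of 20 teachers per school, a drop-out rate of 20% and intra-cluster correlation coefficient of 0.05", and the result is that "the DE for the teacher sample is 1.8, which results in a required sample size of at least 231 teachers".

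The planned enrolment is given just before: "Our target sample will be at least 20 teachers per school, resulting in a total sample of at least 240 teachers". The two totals stand in the same paragraph, so 240 reads as covering 231.

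The Data analysis section specifies intention to treat, with the last observation carried forward for drop-outs.

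**The concern.** Drop-out normally raises the number to recruit. Here it does the opposite: its only role is to make the clusters smaller, which reduces the design effect and so the required number. A design effect built on 16 remaining teachers per school gives a requirement for remaining teachers. The plan sets that number beside the number enrolled, and no step compares it with the number left after drop-out.

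Teacher-reported use of violence is one of the two measures of the primary outcome (Outcome measures). If the stated 80% is not delivered on the plan's own inputs, readers may take a null teacher result as stronger evidence of no effect than it is.

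**Working it through.** **Inputs, all from Participants:** α = 0.05; target power 0.80; f = 0.25 (d = 2f = 0.50 for two equal groups); base requirement 128; 12 schools with at least 20 teachers each (240); drop-out 20%; intra-cluster correlation 0.05. Sidedness is not stated; a 1-df F test is used here.

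**1. Base requirement.** Power comes from the noncentral F with 1 and n − 2 df and noncentrality f² × n. At n = 128 the noncentrality is 0.0625 × 128 = 8.0 and power is 0.801. The 128 is reproduced.

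**2. The plan's 231.**
- Cluster size after drop-out: 20 × 0.8 = 16.
- DE = 1 + (16 − 1) × 0.05 = 1.75, printed as 1.8.
- 128 × 1.8 = 230.4, rounded up to 231: reproduced exactly.
- With the unrounded DE: 128 × 1.75 = 224.

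Nothing is divided by 0.8, so neither 231 nor 224 contains an allowance for lost teachers. Without the drop-out assumption, DE = 1 + 19 × 0.05 = 1.95 and 128 × 1.95 = 249.6, or 250. The drop-out assumption lowered the requirement.

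**3. What 240 enrolled delivers with 20% drop-out.**
- Analysed: 240 × 0.8 = 192, which is 39 below 231 and 32 below 224.
- Effective n: 192 / 1.75 = 109.7, against 128.
- Power at f = 0.25: 0.737. With the rounded DE, 192 / 1.8 = 106.7 and power is 0.725.
- Detectable effect: at effective n = 109.7, f = 0.27 gives power 0.800, so d = 2 × 0.27 = 0.54.

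**4. What 240 delivers if all are analysed.**
- DE = 1.95; effective n = 240 / 1.95 = 123.1; power 0.786.
- In general, with a proportion r retained, effective n = 240r / (0.95 + r). This rises with r and is largest at r = 1, where it is 123.1. At the minimum enrolment, no drop-out rate reaches 128.

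**5. Pupils, by the same method.**
- DE = 1 + (64 − 1) × 0.05 = 4.15; 128 × 4.15 = 531.2, or 532: reproduced.
- Retained: 960 × 0.8 = 768, well above 532. Effective n = 768 / 4.15 = 185.1 and power is 0.92.

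**6. Enrolment needed with 12 schools.** Dividing by 0.8 alone gives 224 / 0.8 = 280 or 231 / 0.8 = 288.75, or 289. With the number of schools fixed, extra teachers enlarge the clusters and raise the DE:

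| Enrolled | Per school | Analysed per school | DE | Effective n | Power |
|---|---|---|---|---|---|
| 240 | 20 | 16 | 1.75 | 109.7 | 74% |
| 280 | 23.3 | 18.7 | 1.883 | 118.9 | 77% |
| 289 | 24.1 | 19.3 | 1.913 | 120.8 | 78% |
| 336 | 28 | 22.4 | 2.07 | 129.9 | 81% |

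About 28 per school are needed for an effective n of 128.

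**The case against.** **Last observation carried forward keeps drop-outs in the analysis.** This is the strongest reply: 192 is a completers figure, and the planned analysis set is everyone enrolled. That stands, but it does not restore 80%. With 240 analysed, 250 are needed and power is 78.6% even if the full effect survives. Carrying forward no change would dilute the effect. If f fell to 0.20 (20% carried forward, SD unchanged; an assumption), power would be about 60%.

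**240 is a floor.** More teachers per school would help, but the plan commits only to 20.

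**The planned test is a time × group interaction.** Its power depends on the pre–post correlation, and a repeated-measures formula could need far fewer than 128 (34 at an assumed correlation of 0.5). A reader might infer from the shortfall that the trial truly cannot reach 80% for teachers. The document does not support that: it gives no correlation. What can be shown is that the requirement it sets, 128 before clustering, is not met on its own inputs.

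**The loss is modest.** It is about 6 points at f = 0.25, and the plan expects moderate to large effects. That stands and bears on severity.

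**Stronger readings.** A reader might go on to test on school-level degrees of freedom, which would lower power further. The plan's calculation adjusts by design effect only, so that is a separate question of method. A reader might also infer that 20 per school is unsecured because the Schools section sets only a pupil-number criterion. But Participants states 20 as a minimum with all teachers included, and nothing in the document suggests fewer.

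**Conclusion.** The point holds. The 231 is a requirement for analysed teachers and is not met by the 192 that the plan's own drop-out leaves from its minimum enrolment. Delivered power at f = 0.25 is about 74%, with a detectable effect of d ≈ 0.54. Counting all 240 gives at most about 79%. Rounding the DE from 1.75 to 1.8 is slightly conservative and does not close the gap.

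These figures rest on the plan's f = 0.25, intra-cluster correlation of 0.05, 20% drop-out, 20 teachers in each of 12 schools, and its between-group base of 128. They concern only the teacher-reported half of the primary outcome. The point should be fixed but is not critical: the shortfall is moderate and no analysis or decision rule changes.

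**What to change.** In the sample-size text of Participants:

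- State the teacher DE as 1.75, and say that 224 is the number of analysed teachers required at 16 per school.
- State the delivered power for the minimum of 240 teachers in 12 schools: about 74% with 20% drop-out, and at most about 79% with all 240 analysed, less if carrying forward no change dilutes the effect. Alternatively, state the detectable effect with 20% drop-out as d ≈ 0.54.
- Recompute the figure with the teachers actually enrolled. The Trial status section reports that recruitment was completed by 30 November 2019.
- Remove the implication that 240 meets the requirement.
- Do not print 280 or 289 as the number to recruit. Under the plan's formula with 12 schools these give 77% and 78%; about 28 per school (336) would be needed.

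The cost is text only. The downside is a less favourable stated power for the teacher measure. The pupil calculation can stay as it is.
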